## Abstract

**Background:**

High-risk percutaneous coronary intervention (PCI) with mechanical circulatory support (MCS) has been associated with varying rates of bleeding due to variable bleeding definitions, incomplete data relative to site-specific bleeding, and inclusion of variable patient populations.

**Study Design and Objectives:**

SAFE-MCS (NCT05077657) is a multicenter, single-arm, open-label study designed to evaluate the safety of complex high-risk PCI using Impella and surveillance with the Saranas Early Bird Bleed Monitoring System (EBBMS). The study aims to enroll 184 evaluable subjects at up to 15 US centers. The primary clinical end point is the incidence of access-site related BARC type III or V bleeding. Secondary clinical end points include the incidence of each of the Saranas EBBMS level 1, 2, and 3 indicators and the incidence of all BARC type III or V bleeding. Enrollment is anticipated to complete in September 2023 with no longitudinal follow-up.

**Conclusions:**

SAFE-MCS is the first study to exclusively assess bleeding complications in patients undergoing PCI with Impella with independent adjudication via a clinical end point committee and will gather meaningful real-world data using contemporary practice.

Periprocedural bleeding is the most common complication in patients undergoing percutaneous coronary intervention (PCI) and is associated with a significantly increased risk of mortality, morbidity, and cost.^1^ Recently, the acuity and complexity of PCI have increased, and the use of mechanical circulatory support (MCS) has expanded,^2^ leading to an inherent increase in procedural and bleeding complications.^3^, ^4^, ^5^, ^6^, ^7^, ^8^ Despite the development and implementation of safe femoral access techniques (including the use of micropuncture needles and direct visualization using ultrasound and fluoroscopy)^9^^,^^10^ as well as adjunctive techniques,^11^ vascular and bleeding complications remain frequent, especially when large-bore devices are used.^1^

Early detection of access-related bleeding complications remains challenging, as clinical recognition mainly relies on the occurrence of signs and symptoms (hematoma, pain, hypotension, and sometimes death) and additional imaging confirmation (ultrasound, computed tomography), which usually occur when bleeding is clinically severe. Early awareness of internal bleeding allows physicians to directly and immediately address this complication and increase postprocedural vigilance in these vascular interventions. The Early Bird Bleed Monitoring System (EBBMS; Saranas) is a novel technology that has been designed to detect the onset and progression of an internal bleed and to provide early notification to clinicians.^12^^,^^13^

## The Saranas Early Bird Bleed Monitoring System

The Saranas EBBMS is a real-time bleed detection system that continuously senses and measures potential changes in regional bioimpedance, which indicates a potential bleeding event. As a fully functional introducer sheath, the EBBMS consists of (1) a vascular access sheath with 4 embedded electrodes positioned along the length of the cannula that form a bioimpedance measurement circuit and (2) a user interface display that houses a printed circuit board assembly running an algorithm that analyzes bioimpedance, which can trigger visible and audible indicators to communicate the state of change in bioimpedance to the physician, as depicted by the larger blood drop symbols (Figure 1).

**Figure 1 fig1:**
[figure not shown]
**The Early Bird Bleed Monitoring System from Saranas.** The system consists of a standard 6F or 8F endovascular access sheath with embedded electrodes and a user interface display, which houses a printed circuit board assembly running an algorithm that analyzes bioimpedance and can trigger visible and audible indicators to communicate the state of change in bioimpedance.

After Saranas EBBMS insertion and activation, baseline bioimpedance readings are collected, and the device detects changes in bioimpedance as a response to an active bleed (Figure 2). The user interface display features a 3-level bleed indicator system that sequentially illuminates light emitting diode (LED) indicators to show an increase in bleed progression at the following levels:•Level 1 indicator (first LED) is triggered by the early onset of a bleed. An audible alert is momentarily activated once this level is triggered.•Level 2 indicator (second LED) is triggered as the bleed progresses when a bioimpedance threshold is reached. An audible alert, longer in duration than the first LED, is momentarily activated once this level is triggered.•Level 3 indicator (third LED) is triggered as the bleed continues to progress further when a higher bioimpedance threshold is reached. An audible alert is activated once this level is triggered and requires the attending clinician to silence the device by pressing the silence button.

**Figure 2 fig2:**
[figure not shown]
**The Early Bird Bleed Monitoring System and relationship between bioimpedance and bleed monitoring.** The Early Bird Bleed Monitoring System provides a bleed detection array via embedded electrodes, continuously monitoring and interrogating changes in regional bioimpedance. It has been demonstrated that there is a consistent correlation between a decrease in bioimpedance and an increase in extravascular fluid accumulation (bleeding).^12^

Prior work in an animal model has demonstrated the performance of the EBBMS (sensitivity and specificity of 100%) in detecting the onset of access-related bleeds as low as ∼50 mL (level 1) and to continuously assess its progression (level 2, ∼100 mL; level 3, ∼200 mL).^12^ A first-in-human study of patients (N = 60) undergoing a variety of elective endovascular procedures demonstrated the safety and accuracy of the EBBMS for the real-time detection and monitoring of access site-related bleeding events. The study demonstrated a high level of agreement between the EBBMS and postprocedural computed tomography to identify periprocedural bleeding events. Indeed, the EBBMS correctly identified bleeding status (bleed or no bleed) in all patients, which included 35% of patients with no bleed and 65% with a bleed, as confirmed by computed tomography. Importantly, among patients with EBBMS-reported bleeding, approximately one-third occurred during the procedure and approximately two-thirds occurred after the procedure.^13^

## Design of the SAFE-MCS study

The Safe Surveillance of PCI Under Mechanical Circulatory Support with the Saranas Early Bird Bleed Monitoring System (SAFE-MCS; NCT05077657) is a multicenter, single-arm, open-label study to evaluate the safety of complex high-risk PCI using the Impella (Abiomed) in conjunction with the Saranas EBBMS. The study will enroll 184 evaluable subjects at up to 15 US centers. Evaluable subjects are defined as all participants who had an EBBMS placed ipsilateral to MCS and had postprocedural monitoring by the EBBMS for a minimum of 2 hours. The study is anticipated to be approximately 24 months in duration. The duration of each subject’s participation will be the duration of the index hospitalization. The study is funded by Saranas, Inc, with an independent clinical events adjudication committee (Cardiovascular Research Foundation) and an independent imaging core laboratory (Medical Metrics).

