### Study procedure

The study is divided into 3 timepoints: preprocedure, day of procedure, and postprocedure. Figure 3 summarizes the study flowchart. During the preprocedure timepoint, the Impella endovascular access procedure will be planned, and an assessment of baseline signs and symptoms will be collected. On the day of the procedure, high-risk PCI with Impella will be performed in accordance with the institution’s standard practice. The Saranas EBBMS sheath will be inserted in the femoral vein, ipsilateral to the Impella device (Central Illustration). Briefly, the data to be collected are the type of coronary intervention under Impella support; type of Impella device; type of Impella sheath; Impella bore sheath size; type of vessel cannulated with the Saranas EBBMS (eg, femoral vein); access technique (eg, ultrasound-guided, micropuncture, anterior vs posterior puncture); investigator’s actions in response to any bleed detection, eg, anti-thrombotic reversal, termination of the procedure, additional imaging, or interventions; and recording of adverse events and/or device complications. If angiograms are performed before and after the large-bore arterial access, these will be sent to the imaging core laboratory for adjudication of any bleeding or safety events.

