## Statistical considerations

### Sample size calculations and assumptions

The primary efficacy aim of this study is to demonstrate the incidence rate of access site-related BARC type III or V bleeding is reduced compared with the historical incidence rate. The secondary efficacy aims are to estimate the incidence rate of activation of each of the EBBMS level 1, 2, and 3 indicators and the incidence rate of all BARC type III or V bleeding and to investigate whether there is an association between the level of indicator and BARC type. The safety aim is to estimate the overall complication/adverse event rate as well as the adverse event rates related to the EBBMS.

The PROTECT II study enrolled 216 patients undergoing nonemergent high-risk PCI under MCS with Impella support.^16^ Investigators reported a major bleeding rate (defined as BARC III or V bleeding) of 12.5%. In the SAFE-MCS study, a 50% reduction in access-site bleeding rate (P) under surveillance with the EBBMS is estimated. The magnitude of reduction was chosen based on what was perceived to be clinically meaningful by the medical trial leadership and took into account that not all bleeding events are access-related and could be reduced by the use of the Saranas EBBMS. Assuming that the rate of bleeding (P) is 6.25%, a sample size of 184 evaluable subjects is required to achieve 90% power for a 1-sample exact binomial test at the 1-sided 0.05 alpha level.

Data will be summarized by sample size (N), mean, standard deviation, minimum, median, and maximum for continuous variables and by sample size and frequency and percentage of discrete variables. For all subjects included in this study, demographics (age, sex, race/ethnicity), medical history, physical examination, and laboratory tests will be summarized.

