### Analysis of primary efficacy end points

The incidence of access-related BARC type III or V bleeding events will be defined dichotomously as bleed or no bleed. The frequency and proportion of subjects with a primary efficacy end point will be calculated along with the upper 95% confidence bound. Success will be based on showing the confidence bound is less than the historical rate of 12.5%

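### The evaluable set on which the primary test is sized requires 2 hours of post-procedure monitoring, so it can leave out early primary events and favour success

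*Protocol article*

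**What the plan says.** Under Design of the SAFE-MCS study, evaluable subjects are those who "had an EBBMS placed ipsilateral to MCS and had postprocedural monitoring by the EBBMS for a minimum of 2 hours". The sample size section uses the same unit: "a sample size of 184 evaluable subjects is required to achieve 90% power", for a "1-sample exact binomial test at the 1-sided 0.05 alpha level". No other efficacy population is defined.

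The primary analysis section speaks only of the proportion of subjects and names no analysis set. Its rule is "Success will be based on showing the confidence bound is less than the historical rate of 12.5"%.

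The Central Illustration legend gives the end point as an in-hospital rate. Table 2 places bleeding that needs surgical control in type 3b and fatal bleeding in type 5, so both are primary events when they are access-site related. The Study procedure section lists possible investigator responses to a detected bleed, including "termination of the procedure, additional imaging, or interventions".

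Nothing in the article says that a subject with a primary event stays in the analysis if monitoring stopped before 2 hours.

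**The concern.** Membership of the evaluable set depends on something observed after treatment, and that something can be linked to the outcome. A subject with a fatal access-site bleed, or one whose sheath comes out early in the course of managing a bleed, may not complete 2 hours of monitoring. By the definition this subject is not evaluable, and because the target is 184 evaluable subjects, another subject takes the place. The event belongs to the in-hospital end point but would not reach the numerator.

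The error runs one way: losing bleeders more often than non-bleeders lowers the observed rate. In a single-arm trial judged against a fixed 12.5%, no concurrent control group undergoes the same selection to offset it. The confirmatory claim is what is at stake.

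**Working it through.** **Inputs from the Protocol article.** n = 184 evaluable; null rate p0 = 12.5%; assumed rate 6.25% ("Assuming that the rate of bleeding (P) is 6.25"%); exact binomial test, one-sided alpha 0.05; success if the upper 95% bound is below 12.5%. The upper bound is taken as the one-sided Clopper-Pearson bound, which matches the exact test.

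**Inputs assumed.** f = share of subjects with a primary event who fail the 2-hour condition; g = the same share among subjects without one. The article gives neither.

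**Step 1: reproduce the design.** P(X ≤ 15 | 184, 0.125) = 0.0416 and P(X ≤ 16 | 184, 0.125) = 0.0686, so success means at most 15 events. Power is P(X ≤ 15 | 184, 0.0625) = 88.5%, close to the stated 90%; the normal approximation gives n = 187. The one-sided 0.05 reading therefore fits. Expected events under the design: 184 × 0.0625 = 11.5.

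**Step 2: false success when the true rate is 12.5%.** The rate among evaluable subjects is

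q = 0.125(1 − f) / [0.125(1 − f) + 0.875(1 − g)],

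and the chance of success is P(X ≤ 15 | 184, q). With g = 0 the denominator simplifies to 1 − 0.125f.

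| f (bleeders lost) | g (non-bleeders lost) | q | Chance of success |
|---|---|---|---|
| 0% | 0% | 12.50% | 4.2% |
| 5% | 0% | 11.95% | 6.5% |
| 10% | 0% | 11.39% | 9.9% |
| 20% | 0% | 10.26% | 20.9% |
| 10% | 5% | 11.92% | 6.6% |
| 20% | 5% | 10.74% | 15.5% |
| 10% | 10% | 12.50% | 4.2% |

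With g = 0, the expected number of lost bleeders per 184 evaluable subjects is 184 × 0.125f / (1 − 0.125f): about 1.2 at f = 5%, 2.3 at 10% and 4.7 at 20%.

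**Step 3: restore lost bleeders to an observed result.** Each restored bleeder adds one to the numerator and one to the denominator.

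| Result | One-sided 95% upper bound | Outcome |
|---|---|---|
| 15/184 | 12.28% | success |
| 16/185 (one restored) | 12.84% | failure |
| 12/184 | 10.35% | success |
| 15/187 (three restored) | 12.08% | success |
| 16/188 (four restored) | 12.64% | failure |

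At the boundary one lost event decides the result. From 12/184, close to the 11.5 expected, it takes four.

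**The case against.** - **The primary denominator is not stated.** The primary analysis section names no set, and the analysis plan, which is not shown, may define another. This stands as a limit: use of the evaluable set is inferred from the sample size section. But it is the only efficacy set the article defines, and the test is sized on it.
- **Bleeding alone removes no one.** This stands. A subject who bleeds, even during the case, is evaluable once monitored for 2 hours. The sheath is in the femoral vein while the Impella access is arterial, and nothing says that an alert or a repair leads to sheath removal. Ending the procedure does not end the monitoring that follows it. The exposed group is subjects who die or whose sheath comes out before 2 hours.
- **The first-in-human timing data do not give the loss rate.** A reader might take "approximately one-third occurred during the procedure and approximately two-thirds occurred after the procedure" as a guide to f. It covers any EBBMS-reported bleed in varied elective procedures, not BARC III or V events, and a bleed during the procedure does not imply under 2 hours of later monitoring.
- **Non-bleeders may fail the condition too.** This stands, and it shrinks or removes the inflation, as the rows with g above zero show.
- **Safety data.** A reader might infer that early device harms also disappear. The article does not support that: the Assessment of safety section computes rates in the study population, and access-site bleeding and death are listed safety end points.
- **The benchmark.** A reader might infer that the 12.5% counts every treated patient. The article reports 216 enrolled patients and the rate, but not the denominator behind it.

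**Conclusion.** The point holds as a conditional one. The only defined efficacy population carries a post-treatment condition, the primary test is sized on it, and no text protects an early primary event from exclusion. If that set is the primary denominator, the definition can bias the rate toward success. It does not follow that bleeders as a group are removed.

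The direction of the bias rests on bleeders failing the 2-hour condition more often than non-bleeders. That is plausible for fatal bleeds and early sheath removal, but the article does not quantify it. The false-success figures are therefore illustrations over an assumed range, not estimates. What they show is that a small loss matters: about two lost bleeders per 184 evaluable subjects, with no loss of non-bleeders, more than double the 4.2% error rate.

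**What to change.** State the primary denominator in the primary analysis section, and make it every enrolled subject in whom an EBBMS was inserted, or insertion attempted, for Impella-supported PCI. Count any in-hospital access-site BARC III or V event in these subjects, whatever the monitoring time. Keep the 2-hour evaluable set for the EBBMS indicator end points, where monitoring time is relevant, and for a sensitivity analysis of the primary end point. Recruitment may still be planned to 184 evaluable subjects. The safety set needs no change on this account.

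The cost is wording in the protocol and analysis plan. Participation already covers the whole index hospitalization, so no new visits are needed. The small downside is that the headline rate may be slightly higher.

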### Study population

The complete inclusion and exclusion criteria are shown in Table 1. Briefly, patients who are ≥18 years of age who plan to undergo a complex and high-risk PCI requiring MCS with an Impella 2.5 or CP (Abiomed) via transfemoral arterial are eligible for the study. The Saranas EBBMS will be used in the ipsilateral femoral vein to monitor bleeding events during the periprocedural period. The study subject will be informed of the nature of the study, agree to its provisions, and provide written informed consent as approved by the institutional review board of the respective clinical site. Key exclusion criteria include absolute contraindications or allergy to iodinated contrast that cannot be adequately treated with premedication; active bleeding; incapacity to safely access the femoral artery or femoral vein; significant femoral, iliac, abdominal, or thoracic aortic disease that precludes placement of MCS; anemia (hemoglobin <9 g/dL), thrombocytopenia (platelet count <50,000 cells/mL), history of bleeding diathesis or coagulopathy, or hypercoagulable states; active infection not controlled with antibiotic therapy; current pregnancy or women of child-bearing potential without documented negative pregnancy test; estimated life expectancy <24 hours; and patient is in cardiogenic shock at the time of enrollment.

**Table 1 tbl1:** SAFE-MCS inclusion and exclusion criteria.

**Inclusion criteria**
Patients must meet the following inclusion criteria to be eligible for the study. • ≥18 y of age • Planned complex high-risk PCI using MCS with Impella from a femoral access and use of Saranas Early Bird Bleed Monitoring System • The study patient has been informed of the nature of the study, agrees to its provisions, and has provided written informed consent as approved by the institutional review board of the respective clinical site.
**Exclusion criteria**
Patients meeting any of the following criteria will be excluded from the study. • Absolute contraindications or allergy to iodinated contrast that cannot be adequately treated with premedication • Active bleeding • Incapacity to safely access femoral artery or femoral vein • Significant femoral, iliac, abdominal, or thoracic aortic disease that precludes placement of MCS • Anemia (hemoglobin <9 g/dL), thrombocytopenia (platelet count <50,000 cells/mL), history of bleeding diathesis or coagulopathy, or hypercoagulable states • Active infection not controlled with antibiotic therapy • Currently pregnant or women of child-bearing potential without documented negative pregnancy test • Estimated life expectancy <24 h • Patient is in cardiogenic shock at the time of enrollment.

MCS, mechanical circulatory support; PCI, percutaneous coronary intervention.

Withdrawal of a subject from the study will be at the investigator’s discretion with consideration of the safety and well-being of the subject. Subjects may withdraw from the study at any point.

### Primary end points

The primary end point is incidence of access-site related bleeding (Bleeding Academic Research Consortium [BARC]^14^ type III or V). For the principal analysis of the primary end point, bleeding events are adjudicated per the BARC bleeding criteria shown in Table 2.

**Table 2 tbl2:** BARC bleeding criteria.

**Type 0:** No bleeding
**Type 1:** Bleeding that is not actionable and does not cause the patient to seek unscheduled performance of studies, hospitalization, or treatment by a healthcare professional; may include episodes leading to self-discontinuation of medical therapy by the patient without consulting a healthcare professional
**Type 2:** Any overt, actionable sign of hemorrhage (eg, more bleeding than would be expected for a clinical circumstance, including bleeding found by imaging alone) that does not fit the criteria for type 3, 4, or 5 but does meet at least 1 of the following criteria: (1) requiring nonsurgical, medical intervention by a healthcare professional, (2) leading to hospitalization or increased level of care, or (3) prompting evaluation
**Type 3a:** Overt bleeding plus hemoglobin drop of 3 to 5 g/dL^a^ (provided hemoglobin drop is related to bleed); any transfusion with overt bleeding
**Type 3b:** Overt bleeding plus hemoglobin drop 5 g/dL^a^ (provided hemoglobin drop is related to bleed); cardiac tamponade; bleeding requiring surgical intervention for control (excluding dental/nasal/skin/hemorrhoid); bleeding requiring intravenous vasoactive agents;
**Type 3c:** Intracranial hemorrhage (does not include microbleeds or hemorrhagic transformation, does include intraspinal); subcategories confirmed by autopsy or imaging or lumbar puncture; intraocular bleed compromising vision
**Type 4:** CABG-related bleeding; perioperative intracranial bleeding within 48 h; reoperation after closure of sternotomy for the purpose of controlling bleeding; transfusion of 5 U whole blood or packed red blood cells within a 48-h period^b^; chest tube output 2L within a 24-h period
**Type 5a:** Probable fatal bleeding; no autopsy or imaging confirmation but clinically suspicious
**Type 5b**: Definite fatal bleeding; overt bleeding or autopsy or imaging confirmation

Platelet transfusions should be recorded and reported but are not included in these definitions until further information is obtained about the relationship to outcomes. If a CABG-related bleed is not adjudicated as at least a type 3 severity event, it will be classified as not a bleeding event. If a bleeding event occurs with a clear temporal relationship to CABG (ie, within a 48-h time frame) but does not meet type 4 severity criteria, it will be classified as not a bleeding event.

BARC, Bleeding Academic Research Consortium; CABG, coronary artery bypass graft.

a Corrected for transfusion (1 U packed red blood cells or 1 U whole blood 1 g/dL hemoglobin).

b Cell saver products are not counted.

